### Therapy protocols and delivery

Refer to Figure 1 for the study flow diagram according to CONSORT guidelines.

**Figure 1 F1:**
[figure not shown]
**GRIN flow chart according to CONSORT guidelines.***Legend:* CP Health: Queensland Cerebral Palsy Health Service; BoNT-A: Botulinum Toxin- Type A; EVGS: Edinburgh Visual Gait Scale; PRT: Pediatric Reach Test; COPM: Canadian Occupational Performance Measure; 1MFWT: 1 Minute Fast Walk Test; GMFM-88 D&E: Gross Motor Function Measure-88, Items D&E; CPQOL-Child: Cerebral Palsy Quality of Life Questionnaire; PTs: Physiotherapists; HEP: Home Exercise Programme.

#### Stage 1: Botulinum Toxin-A injection/s

In accordance with current standard clinical practice, the rehabilitation consultant and physiotherapist will determine muscles to be injected with BoNT-A, following clinical assessment and consultation with the child and their caregiver/s. Muscle selection will vary between participants according to spasticity-related functional impairment and goals of the child and family, as well as from clinical assessment of: gait characteristics (observational gait analysis); resistance to passive stretch (Modified Ashworth Scale [68]); spasticity and dynamic range of movement (Modified Tardieu Scale [69]) and passive range of movement (goniometric and angle finder measures [70]). Dose of BoNT-A will be prescribed according to the Consensus Opinion of the ‘We Move’ Spasticity Study Group (2002), up to a maximum dose of 16 U/kg/body weight, or to a total maximum dose of 400 Units of Botox® (Allergan PLC). Children will receive injections either in theatre under general anaesthetic (100U Botox® diluted in 2 mls of normal saline), or as an outpatient using EMLA cream at the injection site/s (100 U Botox® diluted in 1 ml of normal saline).

#### Stage 2: Serial casting and orthotic prescription

Serial casting will be provided within the three weeks following BoNT-A injections to children with a component of fixed equinus contracture (less than neutral/0 degrees of passive range of ankle dorsiflexion with the knee extended) [7]. Casting will be performed until at least neutral dorsiflexion is achieved. Dose comparisons between study arms will be analysed retrospectively from patient records. Orthoses will be prescribed or modified for each participant by an orthotist as clinically indicated. Moulding for orthoses will occur immediately post BoNT-A for children not requiring casting, and on the day of the last cast fitting for those receiving casting. All orthoses will be available prior to commencement of the rehabilitation block.

#### Stage 3: Physiotherapy intervention

Direct therapy dose for both group and individual models of physiotherapy will be one 60 minute session per week for six weeks (total dose six hours), which is consistent with current funded clinical practice in Queensland. Indirect therapy dose will involve each participant performing three additional individualised, goal-directed activities at home three times a week. Participants will be asked to abstain from any other interventions (e.g. occupational therapy, aquatic therapy) during the rehabilitation phase but can return to their usual therapy following the intervention program. Any therapy or additional structured activity completed during the study will be recorded via a custom-designed questionnaire.

##### Individual therapy

Participants in the individual arm of the study will receive physiotherapy on a one-to-one basis from their usual physiotherapist, who may be located in either a hospital or community out-patient setting.

##### Group therapy

Each group will include at least three participants [38]. If there are insufficient participants to form a group for any recruitment block, additional children with CP (not involved in the study) will be invited to participate. Each additional child will need to meet all study inclusion criteria except they will not have received recent lower limb BoNT-A injections. As for individual rehabilitation, group rehabilitation will be provided in hospital or community settings at a location mutually convenient for each geographical cohort. Group sessions will be directed by one lead physiotherapist with assistance from additional physiotherapist/s, allied health assistant/s or physiotherapy student/s to achieve a minimum ratio of one therapist to three participants. Group dynamics will be encouraged in a variety of ways. For example, children will decide on a name for their group, agree on group rules, receive a team “t-shirt” to wear during sessions and be involved in choosing a theme for the group each week. Activities such as warm up, warm down, stretching and circuit stations will include a combination of group or paired formats. The overall ratio will include a minimum of 60% exercises performed as a group or paired activities and 40% exercises performed simultaneously in a circuit format.

### Content of physiotherapy intervention

Content of the physiotherapy protocol is based on a review of the literature and a clinical practice audit of post BoNT-A rehabilitation providers in Queensland. Exercises have been chosen that require minimal specialised equipment to enable consistent delivery of the program across hospital and community settings. To ensure session structure is the same across both physiotherapy models, a program of suitable exercises and progressions will be provided to treating physiotherapists. Therapists will select and modify exercises to suit each child’s age, intrinsic motivators, individual goals and progression rate. An outline of the session format is displayed in Table 1.

**Table 1 T1:** Example of group and individual physiotherapy session content

**Physiotherapy component**	**Time (minutes)**	**Theoretical rationale**	**Activity examples**
**Warm up activities**	5	Activities have been chosen to prepare the child’s mind and body for the therapy session. In the group model, dynamics will be encouraged by performing games/activities as a group.	• Animal and yoga postures
			• Dancing to music/musical statues
			• Balloon tennis
**Lower limb flexibility**	10	Exercises have been selected to mobilize lower limb joints and muscles through the available range using sustained stretching of agonists injected with BoNT-A for a minimum of five repetitions of 30 seconds duration [71,72].	• In paired long sitting facing each other with feet together, pass the ball between each other (hamstring stretch)
			• Heel dips off the edge of a step (calf stretch)
**Circuit Stations:**		Four stations with one minute rest between each one:	
*Station 1***Functional strengthening**	5	Repetitive, weight-bearing activities have been chosen to improve muscle strength required for functional activities that reflect goals identified via the COPM [36,44]. The focus is on concentric and eccentric muscle activity using body weight resistance. Intensity will be specific to each individual, aiming for 70% of maximum effort, with progression occurring through increasing the number of repetitions or the difficulty of the task (e.g. lower the height of the chair for sit to stand; increase the height of the step for step-ups; increase the speed to complete the activity). Three sets of 10 repetitions is the aim for all participants [73-75].	• Sit to stand
			• Squat to stand
			• Forward and lateral step ups and downs
			• Stair climbing.
*Station 2***Standing and dynamic balance**	5	Activities have been selected to improve the limits of stability in standing tasks relevant to balance goals identified on the COPM.	• Activities in standing where the participant has to reach or squat for an object outside the base of their support
			• Games standing on one leg (SLS) with/without support as required (e.g. dribble a ball around the weight-bearing leg)
*Station 3***Targeted motor control**	5	Individualised activities will be set for each participant to facilitate task practise of functional goals identified on the COPM. Repetition/practise and incremental progression of tasks will occur each week, and through the home programme, to reinforce motor learning [76].	• SLS activities +/− support e.g. dribble ball around standing foot.
			• Kicking to goal (start with large goal area and gradually decrease size).
		*Goal example*:	• Kick ball between 2 people (start with larger ball, decreasing to age appropriate size; progress to kicking ball further to side and increase speed).
		Improve XX ability to kick the ball when playing soccer with friends at school	
		• Be able to make contact with the ball 8 out of 10 attempts	
		• Improve accuracy of kicking to a target (5/10 successful attempts)	
			• Dribble ball around obstacles (e.g. figure of 8 around cones).
*Station 4***Fitness/agility**	5	Activities or games will be carried out to challenge and improve participants’ agility and fitness, aiming for carry-over into physical activity goals (such as being able to run in the playground during school breaks without needing to sit down to rest).	• Timed obstacle races
			• Shuttle runs
			• Relay races.
**Warm down activities**	5	Children will participate in activities that continue to mobilise muscles through range to maximise flexibility, prevent muscle soreness and injury, as well as facilitate reduction in heart rate and temperature to ensure they are in a less aroused state prior to leaving therapy.	• Yoga
			• ‘Simon Says’
			• Songs with actions
**Review of home programme**	10	Review of home programme with each caregiver and participant.	Includes incrementally progressing activities related to the functional performance goals (COPM).

*Key:* BoNT-A: Botulinum Toxin-Type A; COPM: Canadian Occupational Performance Measure; SLS: single leg stance.

### Home exercise programme (HEP)

One key researcher (RT) will design an individualised HEP for each participant. Activities will include part or full task practise of each participant’s key functional goals as identified from the COPM. After the first week, the treating physiotherapist will incrementally progress the HEP activities in liaison with the key researcher as required. Caregivers and/or children will be asked to record the dates, duration and number of repetitions of each activity performed as a HEP, as well as involvement in concurrent activities and/or therapy.

### Treatment fidelity

Physiotherapists providing intervention (group and individual) will be masked to baseline outcome assessments. They will require a minimum of two years’ experience in providing post BoNT-A rehabilitation for children with CP in association with CP Health. In addition, before and during the study, each therapist (and assistants as relevant) will receive face to face or telephone education from the study coordinator (RT) regarding intervention format, content, roles of different staff, exercise and HEP progression. At the start of each rehabilitation block, treating physiotherapists will be provided with standard information for each relevant participant, including the BoNT-A injection date, dose and site/s, baseline musculoskeletal assessment and goals (without score) identified through the COPM. A copy of the physiotherapy protocol will also be provided with suggestions of activities to include in the targeted motor control station, based on each relevant participant/s individualised goals. Physiotherapists will complete a session evaluation form for every participant after each of the six sessions. This includes a summary of activities completed including proportion of time taken on each task. Independent content analysis will determine compliance with the protocol across both arms of the study.

### Outcome measures and procedures

1. **Classification of the sample**

Participants entered into the study will be classified according to:

a) **Gross Motor Functional Classification System** (GMFCS-E&R: [9]):

The GMFCS-E&R is an internationally recognized classification scale for gross motor abilities in children with CP aged two to 18 years ranging from Level I (able to walk independently with limitations in higher gross motor skills) to Level V (unable to sit alone). All children in this study will be ambulant, classified as Levels I-III.

b) **Classification of cerebral palsy:**

Participants will be classified according to motor type/s (primary spasticity), number of limbs involved and unilateral or bilateral distribution [77,78].

c) **Functional mobility:***Functional Mobility Scale (FMS)*

The FMS was designed for children with CP aged four to eighteen years and rates assistive devices required and walking ability at five, 50 and 500 metres which correlate with the child’s ability in the home, school and community settings. The scale ranges from N = does not apply; C = crawling; 1 = uses wheelchair; 2 = uses walker or frame; 3 = uses crutches; 4 = uses sticks (one or two); 5 = independent on level surfaces; 6 = independent on all surfaces [79].

2. **Outcome measures**

Outcome measures will be administered by one physiotherapist (MK) trained and experienced in performing all assessments and one Allied Health Assistant (One Minute Fast Walk Test only). Both assessors will be masked to treatment allocation and previous assessment data. Assessments will be performed at baseline (T1: 0–2 weeks pre BoNT-A injection/s), 10–12 weeks post BoNT-A (T2: on completion of the six week rehabilitation block, efficacy) and at 26 weeks post BoNT-A (T3) to determine medium-term retention of effects. Assessment timeframes are depicted in Figure 1*.* A range of outcome measures will be used across domains of the ICF [13].

2.1 **Body functions and structures**

2.1.1 **Quality of gait:***Edinburgh Visual Gait Score for Cerebral Palsy (EVGS)*

Competence of motor control during gait will be compared to normal values using the EVGS and will be a primary outcome measure for this study. The EVGS is a tabulated scoring system that records 17 joint angles or movements of the trunk and lower limbs during a representative stride. EVGS total score ranges from 0 (best) to 68 (worst) [57]. The EVGS has excellent criterion validity (64% agreement with instrumented gait analysis), repeatability (least significant difference = 3.20 points) and sensitivity to change following surgical intervention (minimal clinically important change: mean score reduction of 4.2 points, range +0.3-8.5) [57-59]. It has good intra-observer reliability which is higher with more experienced observers [23,57,80,81]. Split screen gait analysis will be videotaped simultaneously in the sagittal and frontal planes at the Queensland Children’s Gait Laboratory (QCGL) and independently scored off-site by one physiotherapist (LJ) experienced in EVGS scoring and masked to group allocation, order of assessment and previous data.

2.1.2 **Functional balance***The Pediatric Reach Test (PRT)*

To evaluate the limits of stability in free standing, the forward component of the PRT will be used [63]. In this test, the participant stands with their feet on a line with their dominant arm outstretched at 90 degrees shoulder flexion, holding a pen. Paper is fixed to the wall at the side of the participant who touches the wall laterally to make a mark on the paper at the starting position. The participant is then instructed to reach as far forwards as possible without moving their feet or losing balance. A second mark on the paper is made at this point. The reach is measured as the mean distance reached on three attempts. Correlations between the PRT in standing and laboratory tests of limits of stability is moderate-to-high (r = 0.42 to 0.77). For children with CP, test-retest reliability and interrater reliability range from intraclass correlation coefficients (ICC) of 0.54 to 0.88 and 0.50 to 0.93, respectively [63,82].

2.2 **Activity and participation outcomes**

2.2.1 **Goal attainment:***Canadian Occupational Performance Measure (COPM)*

The COPM [56,83,84] identifies concerns regarding occupational performance and documents changes post BoNT-A rehabilitation [29] and will be a primary outcome measure in this study. It has demonstrated high re-test reliability (ICC 0.76-0.89), sensitivity to change and good content, construct and criterion validity for children with CP receiving BoNT-A [17,85-87]. The COPM will be administered using a semi-structured interview in collaboration with the caregiver/s and participant (dependent on age, cognitive ability and motivation to contribute) [88]. The child-adapted model has three sections: self-care (personal care, functional mobility and community management), productivity (play/school) and leisure (quiet recreation, active recreation and socialisation). Caregivers will be asked to identify three daily activities of concern where they or their child hope to improve after lower limb BoNT-A injections [17,85]. They will rate their perception of their child’s performance and their satisfaction with this performance on a 1–10 ordinal scale. A score change of two or more points is considered clinically significant [56].

2.2.2 **Efficiency of gait:***The One Minute Fast Walk Test (1MFWT)*

The 1MFWT is considered a good discriminator of functional ability for dynamic balance, muscle performance and endurance [60]. The test involves a five minute rest, followed by walking for one minute around a 20 metre oval track at maximum walking speed without running. Children are able use normal walking aids and wear orthoses. Distance is calculated to the nearest metre. The 1MFWT shows concurrent validity with the GMFM with a significant correlation between GMFM-88 score and distance walked (r = 0.92) [60]. Reliability has been established (ICC = 0.97, Standard Error of Measurement, SEM =4.0 m (4.1%)) with a score change of <17% (mean 1.28 m/s, SD 0.42) considered clinically meaningful [46].

2.2.3 **Gross motor ability:***Gross Motor Function Measure (GMFM-88)*

The GMFM-88 is a criterion-referenced measure designed for children with CP aged 0–18 years to assess motor function in five areas [61,62]. Items D (standing) and E (walking, running and jumping) will be administered as study participants are ambulant with goals frequently reflected in these areas. The GMFM-88 has good intra-rater (ICCs 0.92-0.99) and interrater (ICCs 0.87-0.99) reliability [61] and demonstrated validity to reflect change in gross motor function over time (ICCs 0.66-0.79) [89]. A ceiling and floor effect has been reported which highlights caution when interpreting results [61,90]. A change score of 1.3 points (total score), 1.2 points (Dimension D) and 1.6 points (Dimension E) is considered clinically meaningful [91,92]. A change score of 3.99 points further separates a great improvement from moderate or no improvement [91].

2.3 **Contextual**

2.3.1 **Quality of life:***The Cerebral Palsy Quality of Life Questionnaire (CPQOL-Child and CPQOL-Teen)*

The CP QOL-Child [64-66] and the CP QOL-Teen [67] are quality of life assessments designed for children and adolescents with CP aged four to 12 years and 13 to 18 years respectively. Both quantify well-being across seven key quality of life domains relevant to age group. Items are scored on a nine point rating scale, then summed and averaged to generate seven domain scores. The primary caregiver proxy versions will be used in this study as it is anticipated that the majority of children will be less than nine years of age. The CPQOL-Child and -Teen (primary caregiver proxy versions) have demonstrated good internal consistency (−Child: ICC 0.74-0.92; -Teen: Cronbach’s alphas 0.81-0.96), test–retest reliability (−Child: ICC 0.76-0.89; -Teen: ICC 0.29-0.83) and adequate construct validity supported by the pattern of correlations with scales including the Child Health Questionnaire (−Child only), Pediatric Quality of Life Inventory (−Teen only), KIDSCREEN and GMFCS [66,67].

2.3.2 **Qualitative evaluation**

i.) **Caregiver, child and physiotherapist satisfaction**

Post intervention (T2), custom-designed questionnaires will be used to evaluate satisfaction with the physiotherapy rehabilitation format. Questions will be open-ended and answers reviewed by one co-investigator (RT) to determine consistent themes.

ii.) **Child’s motivation and engagement with the physiotherapy intervention**

To evaluate whether there is a relationship between study outcomes and participant’s performance in therapy sessions, treating physiotherapists will be asked to rate each participant’s motivation, engagement and compliance with the physiotherapy exercises after each session using custom-designed five point Likert Scales.

iii.) **Child’s ongoing activity levels and maintenance of goals**

At six months post BoNT-A (T3), each caregiver will complete a custom-designed questionnaire to report their child’s access to ongoing therapy, completion of HEP, structured and un-structured activities, as well as caregiver’s perception of maintenance of goal areas on a ten point Likert Scale.

3. **Adverse events**

Treating physiotherapists will record any adverse events following each physiotherapy session. Adverse events will be classified as: *Mild:* awareness of sign or symptom, but easily tolerated; *Moderate:* discomfort enough to cause interference with usual activity; *Severe*: incapacitating with inability to do usual activity. Standard reporting and follow-up will be adhered to as per current Queensland Health protocol.

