### Criteria for withdrawal/failure to proceed

Children will be classified as failure to proceed if they do not attend a minimum of four hours of direct therapy (<66%), or if they need to be withdrawn from the study due to significant post-injection or other medical complications requiring deviation from the rehabilitation pathway.

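### Adverse-event recording is tied to the six therapy sessions, so as written it gives no recording occasion from T2 to T3 or once a child stops attending

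*Protocol article*

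**What the plan says.** Under Outcome measures and procedures, the adverse events item fixes who records and when: "Treating physiotherapists will record any adverse events following each physiotherapy session". Events are graded mild, moderate or severe, with severe defined as "incapacitating with inability to do usual activity". The item closes with a reference to the health service: "Standard reporting and follow-up will be adhered to as per current Queensland Health protocol".

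Other parts of the article bear on this:

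- Criteria for withdrawal/failure to proceed covers children withdrawn because of "significant post-injection or other medical complications requiring deviation from the rehabilitation pathway". It also covers those who attend fewer than four of the six hours.
- Stage 2 places casting before the therapy block: "Serial casting will be provided within the three weeks following BoNT-A injections".
- Treatment fidelity adds a per-session form: "Physiotherapists will complete a session evaluation form for every participant after each of the six sessions". Its described content is the activities done and the share of time on each; adverse events are not named.
- The home-programme log lists dates, duration, repetitions and concurrent activities or therapy.
- The T2 caregiver questionnaire concerns satisfaction with the therapy format.
- The T3 caregiver questionnaire concerns ongoing therapy, home exercise, activity and maintenance of goals.

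None of these three caregiver instruments is described as asking about adverse events.

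**The concern.** The recording rule is stated outright; it is not inferred from silence. Its trigger is a therapy session, and sessions fill only a short part of the follow-up that the trial sets itself. Where there is no session, the rule produces no entry. An absence of events between T2 and T3 would then be a product of the collection rule and not an observation.

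The same applies to a child who stops coming, because that child has no further session at which anything could be written down. Before the block, an injection or casting event enters the record only if the caregiver or child mentions it weeks later, or if it is still present.

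At stake is the completeness of the trial's description of harms over 26 weeks. With 15 children planned per arm, a few unrecorded events could change that description.

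**Working it through.** The article gives no figure for recording coverage, so there is nothing to reproduce. The check sets the recording rule against the trial's own timeline.

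**Inputs**

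- Sessions: one per week for six weeks (Stage 3: Physiotherapy intervention).
- T2: 10 to 12 weeks after injection, "on completion of the six week rehabilitation block, efficacy" (Outcome measures and procedures).
- T3: 26 weeks after injection (same section).
- Minimum attendance: four of six hours (Criteria for withdrawal/failure to proceed).
- The start of the block is not stated. It is inferred as T2 minus six weeks.

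**Arithmetic**

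- Start of block: 10 − 6 = week 4, to 12 − 6 = week 6.
- Weeks before the block: about 4 to 6. These include the injection and the three-week casting window.
- Weeks from T2 to T3: 26 − 12 = 14, to 26 − 10 = 16.
- Share of follow-up with sessions: 6/26 = 23%.
- Weeks without sessions: 4 + 16 = 20, or 6 + 14 = 20. This is 20/26 = 77% whichever end of the T2 window is used.
- Sessions that may be missed without failure to proceed: 6 − 4 = 2, so attendance can be as low as 4/6 = 66.7%.

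**What the rule captures in each situation**

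- *During the block, child attending.* Covered. The rule says any adverse event, not only those arising in the session, and Table 1 gives ten minutes of every session to reviewing the home programme with caregiver and child.
- *One missed session, child returns.* The event can be recorded at the next session.
- *Child stops attending.* No further recording occasion. If the cause is a medical complication that leads to withdrawal, the withdrawal rule flags it, but it states no grade and places such cases in the same class as poor attendance.
- *Injection and casting period.* Complications that force withdrawal are flagged. Others depend on recall at a session, the first of which falls about 4 to 6 weeks after injection.
- *T2 to T3.* No later session exists, so late recording is not possible. The listed content of the T3 questionnaire does not fill the gap.

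**The case against.** The best case for the plan has four parts.

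First, this is a condensed article. Collection windows and the handling of missed visits commonly sit in the full protocol, which is not shown. That stands as a caution: the gap is in the rule as published, and the full protocol may close it. It does not dispose of the point, because the article states a specific rule, and that rule is narrow if followed.

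Second, the wording is broad about which events count, and the weekly home-programme review gives a natural opening to report them. This stands. A reader might infer that home-programme, injection and casting events, and any event that causes an absence, all fall outside the record. The text does not support that.

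Third, there are other routes. The withdrawal rule can be applied only if the study knows of the complication. The health-service clause is a further route whose content is not shown, so it can neither be credited with closing the gap nor dismissed.

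Fourth, the randomised contrast is group against individual therapy. Injection and casting are not part of it, and after the block children may return to usual therapy. On this view 23% of 26 weeks understates coverage, since recording is planned at every session of the randomised treatment. That is fair as to the contrast between arms. It does not remove the interest in harms up to T3, which the trial itself follows.

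Two stronger readings are tempting. One is that severe events are lost preferentially, because they keep a child away. But an incapacitating event need not outlast a week, and it can be recorded on return or flagged at withdrawal. The other is that the arms would be compared unfairly on safety, because staffing and observation differ. The hypotheses and the Analyses section contain no between-arm safety comparison, and the session form is completed for every participant in both arms. Neither reading is shown by the document.

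**Conclusion.** The point holds in a limited form. As written, the adverse-event rule gives recording occasions in about 6 of 26 weeks. It gives none in the 14 to 16 weeks from T2 to T3 and none for a child who stops attending. Before the block, it leaves events that do not force withdrawal to recall at a session.

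This rests on two assumptions: that the block ends at T2, so that it starts at about week 4 to 6, and that the full protocol adds no other collection point. The 77% is time without a recording occasion. It is not an estimate of the share of events missed, and nothing in the document allows such an estimate. The plan does not contradict itself here. This is a cheap improvement to how harms are ascertained, and it does not affect the primary analysis.

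**What to change.** Keep the session record. Add one fixed caregiver question on adverse events, worded identically in both arms, to three instruments the trial already has: the home-programme log, the T2 caregiver questionnaire and the T3 caregiver questionnaire. Let the first asking look back to the injection and each later one to the previous asking, so that together they cover injection to T3. The T2 and T3 questions also reach families whose child has stopped attending therapy but who still complete those questionnaires.

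Tabulate events descriptively by arm and by period (before the block, during it, and T2 to T3), with the existing three grades. Include the events behind each medical failure to proceed. If the full protocol already does this, one clarifying sentence is enough.

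The cost is one extra question on existing forms and a little data entry, with no new visit or staff. The downside is slightly more caregiver reporting and a higher recorded event count. Events before the block would still rest on recall, but on recall prompted in the same way in both arms.
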